## Abstract

**Background:**

With the relatively high rate of injuries to the lower extremity due to jump-landing movement patterns and the accompanied high costs, there is need for determining potential preventive programs. A program on the intervention of jump-landing technique is possibly an important preventative measure since it appeared to reduce the incidence of lower extremity injuries. In real life situations, amateur sports lack the infrastructure and funds to have a sports physician or therapist permanently supervising such a program. Therefore the current prevention program is designed so that it could be implemented by coaches alone.

**Objective:**

The objective of this randomized controlled trial is to evaluate the effect of a coach supervised intervention program targeting jump-landing technique on the incidence of lower extremity injuries.

**Methods:**

Of the 110 Flemish teams of the elite division, 24 teams are included and equally randomized to two study groups. An equal selection of female and male teams with allocation to intervention and control group is obtained. The program is a modification of other prevention programs previously proven to be effective. All exercises in the current program are adjusted so that a more progressive development in the exercise is presented. Both the control and intervention group continue with their normal training routine, while the intervention group carries out the program on jump-landing technique. The full intervention program has a duration of three months and is performed 2 times a week during warm-up (5-10 min). Injuries are registered during the entire season.

**Discussion:**

The results of this study can give valuable information on the effect of a coach supervised intervention program on jump-landing technique and injury occurrence. Results will become available in 2011.

**Trial registration:**

Trial registration number: NTR2560

## Background

Different studies have pointed out that injuries in jump-landing sports are of frequent occurrence [1-4]. In volleyball, gymnastics and basketball respectively, a total of 2.8 [CI 95%: 2.0 -3.6], 2.2 [CI 95%: 1.6 - 2.9] and 9.8 [CI 95%: 8.5 - 11.1] injuries per 1,000 exposure hours have been reported [5,6]. The majority of the injuries in these sports occur at the lower extremity, accounting for more than 60% of all injuries [2-4]. Both overuse (e.g. shin splints, stress fractures [7], patellar tendinopathy (PT) [8,9], patellar femoral pain syndrome (PFPS) [10,11] and acute injuries (e.g. ACL injury [12-14] and ankle sprains [15-17]) often occur in jump-landing sports.

Sports injuries often are accompanied by pain or other physical discomforts, which in turn result in use of healthcare resources and possibly also in absenteeism from work. The severity of sports injuries can be described based on different criteria including sporting time lost, permanent damage and cost [6]. In a study of Cumps et al. (2007) the number of basketball days for which the athlete was not able to play or train because of the injury sustained was set on 3 to 7 weeks [18]. This means that injury occurrence can put a stop to the athlete's participation in his sport for a long time. From the study of Cumps et al. (2008)[6] it also can be concluded that the direct medical and the indirect costs in Flanders involved in acute injuries only, are respectively 15,027,423 € and 111,420,813 €. No information of the cost of overuse injuries was found, so it can be assumed that the actual cost of both acute and overuse injuries actually is much higher. Even more, important aspects of injury occurrence are the long term consequences. After, for example an ACL-injury or episodes of anterior knee pain, many athletes seem predisposed to osteoarthritis [19-21]. This can already occur at an early age and result in lifelong constraint in sport participation [19,20]. In order to reduce short and long term consequences, there is a need for sports injury prevention.

Arguably the most important injury mechanism for these lower extremity acute and overuse injuries is the jump-landing maneuver [1,3,5]. Proper jump-landing movement patterns are essential to absorb the generated impact forces efficiently, and are suggested to be strongly related to the athlete's risk for injuries to the lower extremity [22,23]. Consequently, various jump-landing related risk factors, such as increased knee valgus during jump-landing technique, ankle instability or a stiff landing technique, appear to be related with injury occurrence [8,24-26]. For example, a stiff landing strategy increases the risk of sustaining injuries due to higher ground reaction forces and decreased shock absorption during landing. Specific movement patterns such as dynamic valgus or stiff jump-landings technique can be a risk factor for respectively ACL injuries and PT [8,24,26,27].

With the relatively high rate of injuries of the lower extremity in jump-landing sports and the severity of these injuries, there is a need for practical preventive programs [28,29]. A program aiming at an improvement of jump-landing technique is potentially an important preventive measure while it is able to target a variety of risk factors for a variety of injuries. Previous attempts have been made to prevent specific injuries through improvement of jump-landing technique, e.g. recurrent ankle sprains [30] and ACL injuries [24]. However, most available prevention programs were supervised by sport physicians or physical therapists. This might work for (sub)elite sports were medical supervision is always available, but amateur sports lack the infrastructure and funds to have a sports physician or therapist permanently supervising such a program. Nevertheless, it is amateur sports where, in absolute sense, the injury burden is highest through high participation numbers. Therefore, the true effectiveness of available preventive programs in this important setting is questionable.

### Objective

The objective of this randomized controlled trial is to evaluate the effectiveness of a coach supervised intervention program targeting jump-landing technique on the incidence of lower extremity injuries.

### Research questions

- What is the effectiveness of a coach supervised jump landing intervention program on the incidence of acute and overuse injuries to the lower extremity?

- What is the effect of a coach supervised jump landing intervention program on jump landing technique of individual athletes?

## Methods

The CONSORT statement was followed to describe the design of this study. This statement is a checklist intended to improve the quality of reports of randomized controlled trials [31].

### Study outline

A two-way cluster randomized controlled trial with a follow-up period of one season (6 months) is used. The participation subjects are athletes from basketball teams of the national divisional, and, 1^st ^and 2^nd ^regional divisional basketball competitions.

The study protocol is accepted by the local ethical committee of the Free University Brussels (B.U.N. B14320071963) and a trial registration number was requested (NTR2560).

This study is financially supported by the Flemish Government through the establishment of the Policy Research Center Sports, Youth and Culture.

### Participants

Athletes who are actively participating in the national division and, 1^st ^and 2^nd ^regional basketball teams in Flanders, Belgium, are eligible for inclusion in the study. Athletes are excluded if they do not master the Dutch language or have a current injury to the lower extremity at time of inclusion.

Written informed consent is obtained from each athlete and the study is conducted in accordance with the ethical institutional rules for human research and in regulation with the Declaration of Helsinki for Medical Research involving human subjects.

### Sample size

A power calculation is carried out for the main outcome variable lower extremity injury incidence. A difference of 50% in the incidence of lower extremity injuries between the intervention and control group after a follow up of one season is considered to be clinically relevant.

The prevalence of lower extremity injuries in basketball in Flanders being about 78% in one season [6], 34 subjects per group are needed to detect the intended difference of 50% in the incidence of lower extremity injuries, with a power of 90% and an alpha of 5%. Assuming a dropout rate of about 20% a total of 82 athletes are needed to detect a potentially clinically relevant effect of the intervention. However, as teams serve as unit of randomization, a cluster effect should be taken into account. Therefore, an intra-cluster correlation coefficient of 20% was considered, resulting in a total of 240 athletes from 24 teams is necessary at baseline.

### Recruitment

Of the 110 Flemish teams of the elite division, 24 teams are included and equally randomized to two study groups (Figure 1). Randomization and group allocation takes place before teams were contacted. This is done in order to avoid any spill over of the intervention while including teams. Through this method blinding of the teams to group allocation is secured.

**Figure 1 F1:**
[figure not shown]
**Flowchart recruitment**.

### Intervention program

After receiving informed consent and baseline questionnaire of a team's individual athletes, trainers are provided with a package that enclosed the necessary information. Control gorup (CG) trainers are provided with a DVD containing general information on the study. Trainers of the intervention teams receive a different DVD with general information on the study and specific information on the intervention program and the individual exercises. Also a written manual including the complete program and a detailed explanation for each individual exercise is provided.

Both research groups continue their regular training routine. Teams of the intervention group (IG) receive an additional intervention program to be carried out during the regular warm-up (Table 1). This program targets at improving the athletes' jump-landing technique.

**Table 1 T1:** Overview of the jump-landing technique program

2 ×/week, **10 min**. 1 min rest between repetitions	Technique/ Month 1			Fundamentals/ Month 2			Performance/ Month 3		
Week 1	Co-contractions	10	L + R	Lying position	15		X-Hops	6	Cycles L + R
	Wall Squat	10		Pelvic bridge	10	sec	Hop-Hop-Hold	8	L + R
	Lateral Jump and Hold	8	L + R	Repeated Tuck Jumps	10	L + R	Mattress jumps	30	sec
	Front Lunges	10		Squat Jump	10		Single leg 90°*	8	L + R
	Step-Hold	8	L + R	Jump Single Leg Hold	8		Max Squat jumps-hold	10	L + R

Week 2	Co-contractions	10	L + R	Pelvic Bridge Single Leg	10		Crossover-Hop-Hop-Hold	8	L + R
	Squat	10		Prone Bridge Hip (EK) Shoulder Flexion	10	L + R	Single Leg 4 Way Hop-Hold*	3	Cycles L + R
	Step-Hold	8	L + R	Side to Side Tuck Jump	10	sec	Single leg 90° Ball*	8	L + R
	Walking Lunges	10		Lateral Hop & Hold	8	L + R	Step, jump up, down, vertical jump	5	L + R
	Lateral Jump and Hold	8	L + R	Hop & Hold	8		Max Squat jumps-hold	10	

Week 3	Squat	10		Single Leg Pelvic Bridge*	10	L + R	Single Leg 4 Way Hop-Hold Ball*	4	Cycles L + R
	Lateral Jump and Hold	8	L + R	Prone Bridge Hip extension	10	L + R	Single Leg 180°	10	L + R
	Single Tuck Jump Soft Landing	10	L + R	Side to Side Tuck Jumps	10	L + R	Jump, Jump, Jump, vertical jump	10	sec
	Lunge Jumps	10		Lateral Hops	10	sec	Mattress jumps	40	L + R
	Lateral Jumps	10	sec	Double leg 90°	8	L + R	Running, Jump down 1 legged, Jump	8	

Week 4	Squat Jumps	10		Single Leg Pelvic Bridge Ball	10	L + R	Single Leg 180°	10	L + R
	Lateral Jumps	10	sec	Prone Bridge Hip Opposed Shoulder Flexion	10	L + R	Jump, Jump, Jump, vertical jump	15	L + R
	Double Tuck Jump	8		Lateral Hops with ball	10	sec	Running, Jump down 1 legged, Jump	10	
	Broad Jump	10	L + R	Single Leg Lateral Hop-Hold	5	L + R	Lay-up ^	10	
	Scissor Jumps	8		Single leg 90°	8	L + R	Height jump ^	10	

*Exercise on the mattress

^ Sport specific jumps for basketball, can be adjusted depending on the sport.

The program is a modification of two prevention programs previously proven to be effective for the prevention of lower extremity injuries [24,32]. The exercises in the current program are adapted so that a more progressive development is present. Furthermore, the materials required to complete the exercises are limited. The program has a duration of three months and is performed twice a week during warm-up (5-10 min). All exercises are selected so that the jump-landing program difficulty is gradually increased. First, basic techniques are practiced and then fundamental exercises are trained. Hereafter, more difficult and sport specific exercises are given in the performance phase. The intervention is considered to be appropriate for all athletes and to have no negative side-effects.

### Measurements

During the study period there are two fixed measurements, at baseline (T0) and after 3 months (T1). At T0 a questionnaire is completed by the athletes, and at both occasions the athletes' jump landing technique is assessed. Additionally, exposure hours and lower extremity injuries are continuously registered during the entire 2010-2011 basketball season (6 months).

#### Questionnaire

At T0 all athletes complete a questionnaire on demographic data, previous injuries, sports history and current sports participation [33].

#### Jump landing technique

An improvement in jump-landing technique is determined by registering jump-landing technique of athletes in the CG and IG. Athletes are asked to perform 3 separate maximal vertical jumps which are recorded on camera (SONY HDV 1080i). The researchers collect the jump-landing data at T0 and T1. These jumps are all analyzed through the computer program Darttrainer^®^. In addition, all jumps are evaluated through a predefined list of criteria, the JLS-System (Jump-landing Scorings system) (Table 2). This tool is developed as a field test to evaluate proper jump-landing technique.

**Table 2 T2:** Scorings system Jump-landing Technique (JLS-system)

Front view (observers view)				
***Criteria***	***Description***	***Observation***	***Measurement***	***Score***

Maintaining 'balance' *- Loss of balance*	Lifting one foot or toes of both feet due to falling.	Observe complete jump	Loss of balance present or not	Loss of balance not present or doubt: 0 Loss of balance present: 1
*- Centre of gravity displacement*		At first foot contact: Perpendicular through incisura jugularis	At maximal knee flexion determine the position of incisura jugularis (left/right) compared to perpendicular	Displacement not present or doubt: 0 Displacement left or right: 1

Landing with '*both feet at the same time'*	Not simultaneous: obviously 2 contact times of the feet visible	Observe complete jump	Simultaneous landing present or not	Simultaneous landing present or doubt: 0 Simultaneous landing not present: 1

*'Muscular control' *during landing	Presence of eccentric control during landing, capacity to lower the body in a controlled manner (no side movements of the knee, no sudden stops)	Observe complete jump	Muscular control present or not	Muscular control present or doubt: 0 Muscular control not present: 1

*'Genu varum' - 'Genu valgum' take-off*	Malalignement: valgus or varus position	At maximal knee flexion: perpendicular from SIAS to ankle (middle of malleoli) - Take-off	No varum or valgum: perpendicular goes through centre of patella	Perpendicular through patella or doubt: 0 Patella lateral from the perpendicular: (1 = varum) Patella medial from the perpendicular: (2 = valgum)

*'Genu varum' - 'Genu valgum' landing*	Malalignement: valgus or varus position	At maximal knee flexion: perpendicular from SIAS to ankle (middle of malleoli) - Landing	No varum or valgum: perpendicular goes through centre of patella	Perpendicular through patella or doubt: 0 Patella lateral from the perpendicular: (1 = varum) Patella medial from the perpendicular: (2 = valgum)

*'Position of feet'*	Feet at shoulder width.	At maximal knee flexion: Perpendicular trough centre of shoulders.	Perpendicular goes trough centre of malleolus internus and externus	Perpendicular through centre of malleoli or doubt: 0 Perpendicular not through centre of malleoli: 1

*'Distance between knees*' compared between initial contact and maximal knee flexion	Distance between knees at maximal knee flexion, 80-110% of distance between knees at initial contact.	Distance between knees at first foot contact and distance between knees at maximal knee flexion.	Range of 80%-110% difference.	Between 80%-11%: 0 Not between 80%-110%: 1

*Hyperpronation - Hypersupination feet* *Take-off*	Inside or outside movement of the malleoli compared to starting position.	Observe complete jump - Takeoff	Compare position feet with starting position.	Hyperpronation or -supination not present or doubt: 0 Hyperpronation or supination present: 1

*Hyperpronation - Hypersupination feet* *landing*	Inside or outside movement of the malleoli compared to starting position.	Observe complete jump - Landing	Compare position feet with starting position.	Hyperpronation or -supination not present or doubt: 0 Hyperpronation or supination present: 1

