### Statistical analyses

The injury incidence density (IID) is calculated as the number of new injuries per 1,000 hours of participation, using exposure time of each individual participant until the first injury. The number of injuries divided by the total time at risk is the preferred measure of incidence because it can accommodate variations in the exposure time of individuals [34,35]. If an athlete suffers multiple injuries, only the first injury will be considered in the analysis.

Because the unit of allocation was teams, we perform a multilevel Cox proportional hazard regression analysis, using the computer based software SPSS 17.0 (SPSS Inc, Chicago, Illinois, USA), to estimate the hazard ratios (HRs) and 95% confidence intervals (CIs). Teams will be used as cluster levels [36].

The difference between the CG and IG regarding the JLS-system is calculated using Repeated Measures ANOVA (p < 0.05) for normally distributed data and the Mann-Whitney-*U *test (p < 0.05) for data which are not normally distributed.

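### Knee varum and valgum are coded 1 and 2, and only tests that read the codes as ordered are named; the plan does not say whether an order is meant

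*Protocol article*

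**What the plan says.** Table 2 of the protocol article (Jump landing technique) has two front-view items on knee alignment, one at take-off and one at landing. Both describe the fault as "Malalignement: valgus or varus position". In the Score column both give "Perpendicular through patella or doubt: 0" and then "Patella lateral from the perpendicular: (1 = varum) Patella medial from the perpendicular: (2 = valgum".

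Two other kinds of item in the table can also fail in either of two directions, and each gives one score for both:
- Centre of gravity: "Displacement not present or doubt: 0 Displacement left or right: 1".
- Feet, at take-off and landing: "Hyperpronation or -supination not present or doubt: 0 Hyperpronation or supination present: 1".

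The remaining categorical items are scored 0 or 1, and the joint angles are recorded in degrees. The article says of the instrument: "This tool is developed as a field test to evaluate proper jump-landing technique". It defines no total score.

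The analysis rule, under Statistical analyses, is: "The difference between the CG and IG regarding the JLS-system is calculated using Repeated Measures ANOVA (p < 0.05) for normally distributed data". For other data it names the Mann-Whitney U test. It gives no method for nominal items and does not say in what form each item is analysed.

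**The concern.** Varum and valgum are deviations in opposite directions from the same neutral position, and the table describes them together as malalignment without ranking them. Both named methods nevertheless read 2 as more than 1: ANOVA as one further unit, Mann-Whitney as a higher rank. Varum becomes the halfway step between neutral and valgum.

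At stake is the second of the article's two research questions, the effect on jump-landing technique. Knee valgus is the first technique-related risk factor that the Background names. A group difference on these items could reflect the numbering of the faults rather than a change in how many athletes land in neutral alignment. The distortion can also run the other way and hide such a change.

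**Working it through.** The article states no figure for these items, so there is nothing to reproduce. The check takes the printed codes and asks what the named tests do with them.

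**Inputs from the article**
- Codes 0, 1 and 2 (Table 2).
- 240 athletes in 24 teams, dropout about 20%, intra-cluster correlation 20% (Sample size).

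**Assumptions**
- All alignment proportions are assumed, because the article gives none.
- Athletes are independent unless stated otherwise.
- One item is compared between arms at T1.

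**1. Change within one athlete**
- Valgum to varum: 1 − 2 = −1.
- Varum to neutral: 0 − 1 = −1.

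The credit is the same, although only the second change ends in neutral alignment.

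**2. A swap with no change in the neutral share**

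Athletes per arm after dropout: 240/2 × 0.8 = 96. Both arms are 50% neutral. Control is 10% varum and 40% valgum; intervention is 30% varum and 20% valgum.
- Control mean: 0.10 × 1 + 0.40 × 2 = 0.9.
- Intervention mean: 0.30 × 1 + 0.20 × 2 = 0.7.
- Share malaligned: 50% in both arms.

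Allowance for teams: 96/12 = 8 athletes per team; design effect 1 + (8 − 1) × 0.20 = 2.4; effective number per arm 96/2.4 = 40.

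Share of simulated trials with Mann-Whitney p < 0.05:

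| Scenario (50% neutral in both arms) | 0/1/2 code |
|---|---|
| 20-point swap, 96 per arm | about 27% |
| 10-point swap, 96 per arm | about 10% |
| 5-point swap, 96 per arm | about 6% |
| 20-point swap, effective 40 per arm | about 14% |

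Scored as malaligned yes/no, where the true difference is zero, the rate is about 5%.

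**3. Dependence on the label order**

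Take 120 per arm with 60% malaligned in both. Control is 20% varum and 40% valgum; intervention is 40% varum and 20% valgum.
- As coded: means 1.00 and 0.80, Mann-Whitney p = 0.087, ANOVA p = 0.063.
- Labels 1 and 2 exchanged: means 0.80 and 1.00, same p-values, direction reversed.
- Malaligned yes/no: 0.60 in both arms, p = 1.0.

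The direction of the apparent effect comes from the numbering alone.

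**4. A gain in neutral alignment that the code hides**

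Control is 40% neutral, 40% varum and 20% valgum; intervention is 55%, 10% and 35%; 96 per arm.
- Control mean: 0.40 × 1 + 0.20 × 2 = 0.80.
- Intervention mean: 0.10 × 1 + 0.35 × 2 = 0.80.
- Rejection: about 7% on the 0/1/2 code, against 56% on malaligned yes/no.

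In this example neutral alignment rises by 15 points and valgum also rises by 15 points. The single code cancels two changes that a reader would want to see separately.

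**The case against.** A reader might infer that the article does analyse these codes as a score, that the two knee items count double in a total, and that a move from valgum to varum is therefore a false improvement. The article does not support that much.

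- **How the items are analysed.** Statistical analyses says only that the group difference "regarding the JLS-system is calculated using Repeated Measures ANOVA" or the alternative test; it does not say which variables enter which test. The bracketed codes, written unlike those of the other items, may be a recording key for direction. This stands, so the point is conditional. It does not remove the problem: if the codes are labels, neither named test suits the item, and if they are a scale, its order is unexplained.
- **Weight in a total.** No total is defined, and the table mixes 0/1 items with angles in degrees. No claim about weight in a total is made here.
- **Valgum may be meant as worse.** The Background links valgus, and not varus, to injury, so the order neutral, varum, valgum can be defended. It would therefore be too strong to say that replacing valgum by varum is no better. What remains is that the article neither states the order nor justifies counting varum as exactly half of valgum.
- **Size.** The 27% needs a 20-point swap with no change in the neutral share. Smaller swaps come close to the nominal 5%, and allowance for teams about halves the figure. This stands, hence the range.
- **Level of detail.** An article may leave item coding to the full plan. Here, however, it prints both the codes and the tests, and the two do not fit together without a further statement.

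**Conclusion.** The point holds as a conditional one. The article gives opposite knee deviations the codes 1 and 2, names only methods that treat 2 as more than 1, and does not say whether the codes are labels or a severity order. If the codes are used as printed, the result on these two items depends on an unstated ordering.

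In the swap scenarios the rejection rate runs from near nominal for small swaps to about 27% for a large one with independent athletes. These figures rest wholly on assumed proportions and show the mechanism; they do not forecast this trial.

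The reach is small: two items of the technique question. The injury outcome and its Cox analysis are not touched. A clarification is desirable before the T1 technique data are compared.

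**What to change.** Do not put the 0/1/2 code into ANOVA or Mann-Whitney. For each knee item, at take-off and at landing, analyse two yes/no outcomes: valgum present or not, as the component of interest given the Background, and any malalignment (varum or valgum) alongside it. Use a method for binary data that allows for teams, such as a mixed or marginal logistic model with team as the cluster. Collapsing to malaligned yes/no alone would not be enough, because it would hide a change in valgum.

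If a severity order was intended, say so and justify both the order and the spacing, and still tabulate neutral, varum and valgum by arm.

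The cost is recoding two items already recorded and a sentence or two in the analysis section; no new data are needed. The small downside is that valgum no longer carries extra weight within a single item score, though it is reported in its own right.
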